### **Patient recruitment**

The study protocol was approved by the Independent Ethics Committee, University of Heidelberg. All patients will be informed about the purpose of the CONTINT trial, the applied surgical strategies, and possible benefits as well as potential risks. Screened patients who have not been enrolled into the trial (including patients unable to give informed consent due to any reason) will be documented in the screening log, including the reason for non-inclusion. In order to be eligible for the trial, patients must be older than 18 years and have given informed consent when undergoing primary emergency abdominal surgery. Their expected survival time should be more than 12 months. Patients requiring primary midline laparotomy for ischemic or infectious disease may be included. While patients with a previous laparotomy are excluded, patients who had previously undergone laparoscopy (except for colon resections) or minor abdominal operations (for example, conventional appendectomy, cholecystectomy, hysterectomy, section) may be included. Furthermore, a septic abdominal focus (for example, perforated stomach ulcer, perforated diverticulitis) must be present.

In addition to these preoperative criteria, the septic source must be successfully controlled and abdominal lavage must be performed prior to intraoperative randomization. When a re-laparotomy is planned intraoperatively (that is, a second look operation), patients may not be included. Patients are excluded from the trial if they are already participating in another trial with interference of the intervention and outcome of this study.

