**Postoperative pulmonary infection**	Infection of the lung with either evidence of increased infection parameters (C-reactive protein > 2 mg/dl and/or leukocytes > 10,0000 cells/ml) that are not caused by a different pathologic process or evidence of pulmonary infiltration in the chest X-ray, requiring antibiotic therapy. Decrease of lung function testing results (forced expiratory volume in 1 s and vital capacity) by 20% or more in comparison with the baseline lung function testing.
**Duration of artificial respiration**	Time on the respirator postoperatively (days)
**Duration of postoperative hemodialysis**	Time on hemodialysis (days)
**Frequency of wound infection**	Surgical site infections within 30 days divided into superficial and deep incisional infections according to the Centers for Disease Control and Prevention definition [14]
**Duration of vacuum therapy**	From first placement of the sponge to removal of the sponge (days)
**Duration of wound healing in patients with secondary wound healing**	From opening of the wound to complete skin closure (days)
**Time to first bowel movement**	From the day of surgery until day of patient’s first bowel movement
**Quality of life**	SF 36 filled in by the patient 30 days and 12 months after the index operation
**Duration of abdominal drainage via intraoperatively placed drains**	From the day of surgery until the day of removal of the last intraoperatively placed drain (days)
**Duration of closed abdominal lavage**	From the day of surgery until the last day of closed abdominal lavage via the intraoperatively placed drains (days)
**Postoperative duration of hospital stay**	From the day of the operation until the day of discharge (days)
**Postoperative duration of intensive care unit stay**	Time from admission to the intensive care unit until transfer to the regular ward (days)
**Mortality**	Death due to any cause at any time during the follow-up period

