## Discussion

The optimal strategy of abdominal wall closure after midline laparotomy has remained an issue of ongoing discussion. To date, various RCTs and meta-analyses on abdominal wall closure strategies after midline laparotomy have been published with heterogeneous results. A recent meta-analysis identified several RCTs on techniques and materials of abdominal wall closure after elective laparotomy [20]. While some of the detected studies included patients who underwent emergency laparotomy, there were no trials that specifically enrolled patients who had emergency surgery. The pooled analyses demonstrated a benefit of the continuous suture technique on the development of incisional hernia. Remarkably, statistical heterogeneity of the meta-analyses increased substantially if studies that enrolled patients with emergency laparotomy were included, whereas there was almost no heterogeneity in the sensitivity analyses excluding these studies. These findings suggest a significant difference between the biological properties of and demands to the abdominal wall of patients undergoing elective and emergency laparotomy. Reasons for this difference have not been clarified in detail and probably include factors such as a contaminated operative field, poor general conditions of these (septic) patients and different requirements to the abdominal wall, especially in patients requiring prolonged mechanical ventilation. In particular, the proliferation of bacteria in tissue represents a strong risk factor causing wound infection with delayed healing of the wound and wound dehiscence [23]. The adverse impact of emergency surgery on the incidence of postoperative complications as compared to an elective setting has already been demonstrated in various studies [24-28]. In a large cohort study including more than 4.800 patients who underwent open gastrointestinal surgery, emergency surgery was associated with a significantly increased incidence of postoperative tissue and wound complications [24]. On multivariate analysis, male gender, peritonitis, kind of operation and multiple operations were independent predictors of tissue and wound complications in the subgroup of patients who underwent emergency surgery.

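### Hospital stay, intensive care stay, ventilation and dialysis are defined without regard to death, so their descriptive comparison can mislead if early mortality differs between arms (minor)

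*Protocol article*

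**What the plan says.** The secondary endpoints are in Table 2 of the protocol article, under Endpoints. Four of them measure time in care or on support:

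- Intensive care stay: "Time from admission to the intensive care unit until transfer to the regular ward (days".
- Hospital stay: "From the day of the operation until the day of discharge (days".
- Ventilation: "Time on the respirator postoperatively (days".
- Hemodialysis: "Time on hemodialysis (days".

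None of the four definitions mentions death. Mortality is a row of its own, "Death due to any cause at any time during the follow-up period", and is not combined with them.

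The Data analysis section says that secondary variables are tabulated and tested, with results read descriptively only. Its rule for missing values concerns the primary outcome.

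On the population, Patient recruitment states: "Furthermore, a septic abdominal focus (for example, perforated stomach ulcer, perforated diverticulitis) must be present". The Discussion refers to the "poor general conditions of these (septic) patients".

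**The concern.** Each definition meets death in one of two ways.

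- **The end event never happens.** A patient who dies in intensive care is not transferred to the ward, and one who dies in hospital is not discharged. Read literally, the definition gives that patient no value, so the comparison is among survivors, a group formed after randomization.
- **The count stops.** Days on the respirator or on dialysis stop accruing at death. A patient who dies soon after surgery while on support scores as having needed little of it.

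Death during the hospital stay is foreseeable in septic emergency patients, and the trial counts it as an endpoint. If the two closure strategies differ in early deaths, a table could show fewer ventilator or intensive care days in one arm for a reason that has nothing to do with faster recovery. What is at stake is how these four secondary results are read.

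**Working it through.** The plan gives no figure to reproduce here: no mortality rate, length of stay or duration of support. Apart from the arm size, every input below is assumed.

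**1. Arm size.** The interim analysis takes place at 80 evaluable patients, and allocation uses balanced blocks: 80 / 2 = 40 per arm.

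**2. Ventilation, count stopped at death.** Assume that every survivor is ventilated for 8 days. One arm has no deaths. In the other, k patients die on day d while ventilated.

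Mean in the arm with deaths = [(40 − k) × 8 + k × d] / 40

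- k = 4, d = 2: (288 + 8) / 40 = 7.4, against 8.0. The arm with four deaths looks 0.6 days better.
- k = 1, d = 2: (312 + 2) / 40 = 7.85. k = 8, d = 2: (256 + 16) / 40 = 6.8. The apparent gain runs from 0.15 to 1.2 days.
- k = 4, d = 8: (288 + 32) / 40 = 8.0. No difference.
- k = 4, d = 20: (288 + 80) / 40 = 9.2. The arm with deaths now looks worse.

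Early deaths flatter the arm. Deaths after long support do the opposite.

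**3. Intensive care stay, deaths without a value.** Assume a stay of 8 days in all survivors of the arm with four deaths. Its mean is 36 × 8 / 36 = 8.0. In the other arm the four comparable patients survive and stay L days: mean = (36 × 8 + 4 × L) / 40.

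- L = 8: 8.0 against 8.0. No bias.
- L = 20: (288 + 80) / 40 = 9.2 against 8.0. The arm with deaths looks better.
- L = 4: (288 + 16) / 40 = 7.6 against 8.0. The arm with deaths looks worse.

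Dropping deaths matters only if those patients would have had different stays.

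**4. The same contrast with variable stays.** In a simulation the underlying stay is identical in both arms (lognormal, median 5 days, mean 7.5), so the true difference is zero. Time to death is exponential. Where death is tied to long stays, half of the patients with the longest stays die, the share being set to give the stated death rate. Entries are mean days in the arm with fewer deaths, then in the arm with more.

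| Handling of death | 5% vs 10% die | 10% vs 20% die | 10% vs 30% die |
|---|---|---|---|
| Cut at death, tied to long stays, mean time to death 3 days | 6.33 / 5.84 | 5.84 / 5.29 | 5.83 / 5.04 |
| Same, mean time to death 10 days | 6.63 / 6.34 | 6.34 / 6.09 | 6.35 / 5.97 |
| Cut at death, unrelated to stay, mean time to death 3 days | 7.24 / 6.98 | 6.98 / 6.45 | 6.96 / 5.92 |
| Same, mean time to death 10 days | 7.34 / 7.18 | 7.18 / 6.88 | 7.19 / 6.55 |
| Deaths dropped, tied to long stays | 6.51 / 6.16 | 6.15 / 5.90 | 6.15 / 6.02 |

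Cutting at death produces a spurious gap of 0.16 (7.34 − 7.18) to 1.04 days (6.96 − 5.92). Dropping deaths produces 0.13 (6.15 − 6.02) to 0.35 days (6.51 − 6.16), and none when death is unrelated to stay. In this set-up death can only shorten a stay, so the uniform direction of the cut rows is built in. Step 2 shows that it can reverse.

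**5. A measure that includes death.** Take days alive and free of ventilation to day 30, with death by day 30 scored 0. With the inputs of step 2 and k = 4, survivors score 30 − 8 = 22. The means are (36 × 22 + 4 × 0) / 40 = 19.8 against 22.0. The result is the same whether the deaths fall on day 2, 8 or 20.

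**The case against.** The strongest reply is that this is a journal article. The value given to a death in a secondary duration is the kind of detail that a full protocol or analysis plan settles, and neither is shown. That is fair as far as an omitted rule goes. It does not answer the point about what Table 2 does fix: end events that a dying patient cannot reach, and raw counts that death cuts off. An unseen rule could repair this, but it would be adding to or overriding the stated definitions.

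Several further points stand and limit the concern:

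- Bias between arms needs unequal early mortality, and nothing in the document makes that likely for two suture strategies. Eligibility also leans against early death: "Their expected survival time should be more than 12 months", together with source control before randomization. These criteria reduce early deaths but do not exclude them.
- The secondary results are descriptive and mortality is reported in the same table, so a reader would see an imbalance in deaths.
- Scoring death as 0 is a choice. It merges mortality with resource use and gives a death on day 2 the same value as a survivor still on support at day 30.

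A reader might infer that the arm with more deaths will look better on all four endpoints. The documents do not support that: for the two stays the bias can be nil or go either way, and for ventilation and dialysis late deaths can reverse it. Nor do they support calling these the trial's main measures of recovery. Table 2 lists 19 secondary endpoints without ranking them, among them quality of life, wound healing and time to first bowel movement.

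**Conclusion.** The point holds in a limited form. As defined, hospital and intensive care stay compare survivors only, and ventilation and dialysis count an early death on support as short support. If early mortality differs between arms, the descriptive comparisons can be biased. For ventilation and dialysis the bias usually favours the arm with more early deaths. For the two stays it appears only if those who die would have stayed longer or shorter than the others.

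Under the inputs assumed here the spurious difference is mostly a fraction of a day and reaches about one day in the more extreme cases. Those inputs (death rates, timing of death, length of stay) do not come from the document, so the figures show the mechanism and a plausible range, not an estimate for this trial. The primary endpoint, the sample size and the interim decision rules do not depend on these variables. Importance is minor.

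**What to change.** Keep the four raw durations. Label hospital and intensive care stay as among survivors, and present all four next to mortality by arm.

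Add, as the between-arm comparison, days alive and free of ventilation, days alive and free of dialysis, and days alive and out of intensive care, each to day 30 with death by day 30 scored 0. Add days alive and out of hospital to day 30 only where readmission dates are available; the article does not say that they are collected. Day 30 is already a scheduled visit. Fix the definitions in writing before any data are analysed by arm.

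Adding is preferable to replacing the four endpoints, because the Trial implementation and status section reports 73 patients already randomized.

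The cost is a little more analysis, values that are less familiar than length of stay and stop at day 30, and a composite that mixes death with resource use. The article does not state that start and stop dates of support are recorded. Where all support falls within the first 30 days, the recorded duration and the date of death are enough: 30 minus the duration for survivors to day 30, and 0 for deaths by day 30.

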### **Standardized treatment**

Patients’ intraoperative and perioperative treatment is standardized except for the closure of the abdominal wall, which is carried out according to the allocated study intervention. Antibiotic prophylaxis and therapy is carried out according to local standards (for example, see [15]).

Electric cautery is used to cut skin, the subcutaneous tissue and the abdominal fascia, carefully avoiding damage to the umbilicus [16]. Opening of the abdomen is performed with scissors and incision of the peritoneum is completed with electric cautery. The performed surgical intervention depends on the underlying disease and is performed in line with local standards. In case of a septic focus (for example, a perforated diverticulitis or perforated gastric or duodenal ulcer), source control and abdominal lavage are essential parts of the procedures. Abdominal drains are placed at the end of surgery. Furthermore, drains may be placed for postoperative continuous lavage. Creation of a stoma is not an exclusion criterion for this trial.

### **Trial interventions**

Before closure of the abdominal wall, the length of the fascial incision is measured (in centimeters)*.* Then, four Mikulicz clamps (or equivalent) are placed at the edges of the abdominal fascia. The expertise of the surgeon (board certified versus no certificate) present at the closure is documented.

In the continuous group, the abdomen is closed by a continuous, all-layer suture using two Monoplus® loops, which are made of a slowly absorbable monofilament material. Monoplus® sutures need to be stretched once by the assisting nurse or operation technician before use to avoid breakage of the material. The first stitch has to be anchored cranial and caudal of the incision. After having closed half of the wound, one end of the loop is cut right below the needle. Then one stitch is made back to the opposite edge of the fascia and both ends are tied with at least four counter-rotating knots. At the caudal end of the wound, the same procedure is done with intersection of both loops at the middle of the incision and overlapping of both suture lines for at least 2 cm. Loops are not to be tied together. For every patient, two loops must be used, irrespective of the length of the wound. After completion of the fascial closure, the loop will be cut directly underneath the needle. The length of the remaining suture material has to be measured.

In the interrupted group, patients will receive abdominal wall closure by interrupted sutures using Vicryl® sutures. Anchoring of stitches cranial and caudal of incision is performed in analogy to the continuous suture group. Suturing of the abdominal wall is performed from either end of the incision to the middle of the incision. The number of sutures used has to be recorded. Once all stitches are done, each suture is tied with at least four counter-rotating knots.

For both groups, the maximum distance between the stitches should be 1.5 cm and the distance from the edge of the fascia should be at least 2 cm. Subcutaneous tissue is not sutured and no subcutaneous drainage is used. The skin is closed with clips and the length of the skin incision (in centimeters) is measured*.*

### **Assessment of safety**

Occurrences of events concerning the primary or secondary endpoints are assessed as endpoints only (not as adverse events) and are explicitly asked for.

The following conditions are expected after the initial operation and will therefore not be classified as a complication: pain, nausea, vomiting, urinary tract infection, hyper- or hypotension, imbalances of blood sugar or electrolytes and other laboratory values out of range, if they are not exceeding the duration and extent that can be expected after surgery.

From the day the patient has signed informed consent until the regular end of the trial at 12 months follow-up or until premature withdrawal of the patient, all serious adverse events (SAEs) must be reported within 5 days after the SAE is known. The SAE form contains the following information: identification of the trial participant, attending physician, description of the SAE (event, beginning and duration, severity, outcome, causality to the intervention of the trial, treatment or interventions taken), date and signature of the attending physician.

Analysis of safety-related data will be based on these SAE reports.

### **Randomization and blinding**

Patients will be randomized to one of the two treatment groups just before closure of the abdominal wall using sealed envelopes. Randomization numbers will be allocated to the two groups in balanced permuted blocks using the random number generator of the validated software SAS by the Institute of Medical Biometry and Informatics (IMBI), Heidelberg, Germany. To avoid any potential of predicting group allocation for patients, the block length is fixed in a separate document that is withheld from the study site. As performed in previous studies, sealed and opaque envelopes are produced and labeled with the randomization number containing a data sheet that states the group allocation for the patient with the respective randomization number [17-19]. Randomization envelopes will be used in consecutive order. To avoid manipulations, a thick black bar was placed on the opposite side of the sheet, exactly at the position where the randomization information is located. Basic characteristics of the patient and day of randomization are documented on the data sheet. Thus, compliance to the randomization scheme may be controlled retrospectively. When the study is finished, all unopened envelopes will be sent back to the data management center where they are compared to the allocated randomization numbers and checked for completeness.

The assessors of the CONTINT trial are blinded to the patients’ study treatment.

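### As described, the patient appears to be tied to the randomization number only after the envelope is open, so the stated checks would not by themselves reveal an envelope opened, held and reused for a later patient

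*Protocol article*

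**What the plan says.** All references are to the protocol article.

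- **Timing of allocation** (Randomization and blinding): "Patients will be randomized to one of the two treatment groups just before closure of the abdominal wall using sealed envelopes".
- **Content of the envelope** (same section): it is opaque, sealed and labeled with the randomization number, "containing a data sheet that states the group allocation for the patient with the respective randomization number".
- **Record, and the conclusion drawn from it** (same section): "Basic characteristics of the patient and day of randomization are documented on the data sheet. Thus, compliance to the randomization scheme may be controlled retrospectively".
- **Other envelope controls** (same section): "Randomization envelopes will be used in consecutive order". At the end of the study, "all unopened envelopes will be sent back to the data management center where they are compared to the allocated randomization numbers" and checked for completeness. A black bar on the back of the sheet guards against reading the arm through the paper.
- **Eligibility settled during the operation** (Patient recruitment): source control and lavage must come before randomization, and "When a re-laparotomy is planned intraoperatively (that is, a second look operation), patients may not be included".
- **Screening log** (Patient recruitment): screened patients who are not enrolled are listed with the reason.
- **Monitoring** (Data management and monitoring): the monitor checks consent and the eligibility criteria, and each center has a close-out visit.

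**The concern.** The sheet that receives the patient's details is the sheet that shows the arm, and it lies inside the sealed envelope. Unless something is recorded elsewhere first, the entry is made with the allocation in view. It then shows who finally received the number, which need not be the patient on the table when the seal was broken.

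This matters because the trial is open label, randomization takes place in the operating room, and the last eligibility criteria are judged there. If a team sees the arm, decides against inclusion and keeps the envelope for the next patient, the two arms can come to differ in baseline risk. The planned analysis would not repair that. The full analysis set contains randomized patients only, so a withheld patient never enters it. The logistic model adjusts for BMI and age but not for the severity of peritonitis, although the Mannheim Peritonitis Index is recorded at baseline (footnote to Table 1).

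**Working it through.** The article gives no figure to reproduce on this point. The check is first one of procedure and then an illustration of size.

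**Step 1. Which departures the described checks can show**

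| What happens to the envelope | Trace left by the described checks |
|---|---|
| Skipped, left sealed | Unopened number below a used one; found on return |
| Opened and discarded | Number with neither a patient nor a returned envelope |
| Used out of order | Day order disagrees with number order |
| Wrong arm given | Arm disagrees with the randomization list |
| Opened, held, used for a later patient | None: number, order, day and arm all agree |

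The last row follows from where the entry is made. The later patient's details and day go on the sheet with the next number in sequence.

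**Step 2. A simulation of the same logic**

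Assumed inputs, none from the article: one list with blocks of 4, 80 patients, half of all candidates of an unfavoured type, and a fraction q of these withheld when the next envelope shows one particular arm; 2,000 runs for each setting. The audit looked for gaps in the numbers and for days out of order.

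- Opened and discarded, q = 0.10, 0.25, 0.50: flagged in about 87%, 99.8% and 100% of trials.
- Held and reused, same q: flagged in 0% of trials. This holds by construction and only confirms Step 1.
- Expected imbalance in the unfavoured type under hold and reuse = 0.5 − 0.5(1−q)/[0.5(1−q)+0.5] = 2.6, 7.1 and 16.7 percentage points (simulated: 3.0, 7.7 and 16.7).

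**Step 3. Possible effect on the primary comparison**

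Inputs from the article: 80 evaluable patients at the interim analysis, taken as 40 per arm, and early rejection at one-sided 0.0115 (Interim analysis). Assumed: a share h of candidates is high risk, with event risk 0.60 against 0.30 for the rest; a fraction f of the high-risk candidates is withheld from one arm; there is no treatment effect.

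- High-risk share in the depleted arm: s = h(1−f)/[h(1−f) + 1 − h].
- Event rates: 0.30 + 0.30s in the depleted arm and 0.30 + 0.30h in the other.

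Lower case, h = 0.2 and f = 0.25: s = 0.15/0.95 = 0.158; rates 0.347 and 0.360; difference 1.3 points.

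Upper case, h = 0.3 and f = 0.5: s = 0.15/0.85 = 0.176; rates 0.353 and 0.390; difference 3.7 points.

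Probability of early rejection in favor of the depleted arm, by the normal approximation to the two-proportion test: P(Z > (2.273·SE0 − d)/SE1). Here d is the difference, SE0 the pooled standard error and SE1 the unpooled one.

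- Lower case: (2.273 × 0.1069 − 0.0126)/0.1069 = 2.155, giving 0.0156.
- Upper case: (2.273 × 0.1080 − 0.0371)/0.1080 = 1.932, giving 0.0267.

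Without selection the probability is 0.0115.

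**The case against.** The strongest reply is that the article claims no more than control of compliance with the randomization scheme. Number, patient, day and arm on the sheet do serve that, together with consecutive use and the return of unopened envelopes. This stands for order, completeness and agreement of arm with the list.

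A reader might infer that the control cannot detect enrolment decided after seeing the arm, whatever form it takes. The documents do not support that. Discarded, skipped and out-of-order envelopes would show. A consented patient dropped at the table should appear in the screening log with a reason, serious adverse events are reportable from signed consent, and the monitor looks at consent and eligibility. Judging source control or lavage only after opening would itself breach the protocol. These controls leave a trail, but none records when an envelope was opened, and the article does not say that the log is compared with the envelopes.

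Three further points are fair and limit the weight of the finding:

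- The timing of the entry is inferred. The article does not say when the sheet is filled in, and the full protocol or site instructions may already require a step before opening.
- The magnitude is assumed. It needs centers to withhold in the same direction, while the Background reports a lack of consensus among surgeons. It also uses an unadjusted test in place of the planned logistic model.
- Stage 1 was nearly filled: 73 patients were randomized at submission, against 80 evaluable patients for the interim analysis.

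**Conclusion.** The point holds in limited form. As described, the patient appears to be linked to the number only once the arm is visible, and one route, an envelope opened, held and reused, would pass every envelope check the article lists. The statement that compliance can be controlled retrospectively therefore reaches further than the record does on this route, and only on this route.

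The effect on the result is unknown. Under the assumed inputs it is small: 1.3 to 3.7 percentage points in expected event rates, and an early-rejection probability of about 1.6 to 2.7% in place of 1.15%. Nothing in the article suggests that such selection occurred, and it should not be read as evidence that concealment failed. The conclusion rests on the inference that no entry is made before opening. If the full protocol contains one, stating it would settle the point. Otherwise this is a cheap improvement worth making, mainly for patients still to be randomized and for a possible second stage.

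**What to change.** **For remaining and second-stage patients.** Amend Randomization and blinding so that, before the seal is broken, the site writes the patient identifier, date and clock time on the outside of the envelope. The site also confirms there that the intraoperative criteria already listed under Patient recruitment are met. From that moment the patient counts as randomized and stays in the full analysis set. Opened envelopes are kept with their sheets and reconciled with the screening log, in addition to the existing return of unopened ones.

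**For patients already randomized.** Compare the dates on the sheets with the screening log, looking for patients logged as not included at the operation shortly before an envelope was used. This cannot be conclusive but needs only existing records. Limit the statement on retrospective control to order, completeness and agreement of arm with the list.

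**Cost.** A label on the remaining envelopes, a short protocol change, about a minute in the operating room and a little reconciliation work; no extra staff or system. Because few stage 1 patients remained, the change can do little for the interim result.
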